### Outcome measures

2.7

Primary outcomes include

(1)blood flow curve and(2)blood PU of relevant sites along the Heart and Lung meridians.

### Safety assessment

2.8

Adverse events should be recorded and assessed by the investigators during the trial. If serious adverse events occur, the researchers should report them to the principal investigator and ethics committee immediately.

### Quality control

2.9

Prior to the trial, this protocol has been modified according to suggestions from experienced acupuncturists. All researchers will undergo a series of training sessions on the purpose and standard operating procedures of the trial. Monitors will verify case report forms as well as the LDF examination procedure during the study. Dropouts and withdrawals including the reasons will be documented in details throughout the trial.

### Data collection and statistical analysis

2.10

Statistical analysis will be performed using the statistical software package SPSS 17.0 for Windows (SPSS Inc., Chicago, IL) by third party statisticians who does not participant in this trial. Numeric data with normal distribution will be expressed as mean ± standard deviations, whereas data with skewed distribution as median with 95% confidence intervals. Categorical data will be shown as counts and percentages.

Repeated measures ANOVA will be used to assess change in continuous variables before and after intervention. The paired samples *t*-test will be used to compare the changes within the groups, whereas the independent samples t-test will be employed for comparisons between the groups. Within-group/between-group comparison regarding data with skewed distribution is assessed using non-parametric test. Between-group differences for baseline dichotomous variables, such as gender and ages, will be tested using the Chi-square test. A *P* value of less than .05 will be considered statistically significant.

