### Study design

2.1

We will conduct a prospective and clinical controlled trial. All participants will be divided into the healthy control group, CSAP group and healthy intervention group. The standard protocol items including Recommendations for Interventional Trials and the Standards for Reporting Interventions in Clinical Trials of Acupuncture guidelines will be followed during the development of this trial protocol. The study design flowchart is shown in Figure 1 and the schedule of enrolment, interventions and assessments is displayed in Table 1.

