#### Procedures for LDF examination and moxibustion

2.6.1

A four-channel LDF (PeriFlux System 5000, Sweden) will be used to measure the microcirculatory characteristics of the Heart and Lung meridians, which could monitor 4 measurement sites simultaneously. The participants will be asked to stabilize for 15 minutes in a supine position in the experimental room before LDF examination. They will be informed to keep silent and normal breath and avoid limb movement during the whole measurement period. The probes will be placed at corresponding measurement sites. Blood flow curve and microcirculatory flux, expressed as blood perfusion units (PU), will be assessed.

(1)Healthy control group and CSAP groupThe probes will be left at 4 measurement sites (Fig. 2), which include “Shenmen” (HT7) and “Shaohai” (HT3) of the Heart meridian, “Taiyuan” (LU9) and “Chize” (LU5) of the Lung meridian. The blood flow curve and PU will be recorded for 5 minutes.(2)Healthy intervention groupTwo sessions of moxibustion will be performed in the Heart meridian and Lung meridian, respectively. The washout period between the two sessions is at least one day to avoid inter-experiment interference. The intervention procedures and LDF measurement sites are shown in Figure 3.

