**Figure 3 F3:**
[figure not shown]
The intervention procedure of the healthy intervention group. (A) Moxibustion site of the Heart meridian and LDF measurement sites of the Heart and Lung meridians; (B) Moxibustion site of the Lung meridian and LDF measurement sites of the Heart and Lung meridians. CSAP = chronic stable angina pectoris, LDF = laser doppler flowmetry.

(1)Intervention in the Heart meridian: By igniting the moxa stick and inserting it into a homemade moxibustion holder to adjust appropriate angle and height, moxibustion will be performed at “Shaohai” (HT3) of the Heart meridian for 15 minutes. During moxibustion, LDF probes will be placed in three measurement sites, which include the midpoint of the Heart meridian along the left forearm (ie, midpoint of between HT3 and HT7), “Chize (LU5)” of the Lung meridian, and the midpoint of the Lung meridian along the left forearm(ie, midpoint of between LU5 and LU9). The intervention procedure and LDF measurement sites are shown in Figure 3 (A). The measurement time points include 5 minutes before moxibustion, 15 minutes during moxibustion and 5 minutes after removal of moxibustion.(2)2)Intervention in the Lung meridian: The moxibustion acupoint is “Chize” (LU5) of the Lung meridian. The LDF examination, moxibusition procedure and measurement time points are the same as 1). During moxibustion, the LDF probes will detect the blood perfusion in three measurement sites, which include the midpoint of the Lung meridian along the left forearm(i.e. midpoint between LU5 and LU9), “Shaohai” (HT3) of the Heart meridian, and the midpoint of the Heart meridian along the left forearm (i.e. midpoint between HT3 and HT7. The intervention procedure and LDF measurement sites are shown in Figure 3(B).

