Second, our study design presents different comparisons to verify the specificity for the meridian-visceral association and site-to-site association between 2 specific meridians, which is a highlight. The theory of meridian-viscera association emphasizes the diagnostic and therapeutic values based on the mutual relation in physiology and the interaction effect in pathology between meridians and viscera. In details, visceral physiological functions and pathological changes will manifest in the corresponding meridians or the acupoints^[33]^ and the visceral disorders can be treated with the involved meridian and acupoints.^[34]^ A number of modern studies have confirmed the relatively specific relationship between meridians and viscera, and the modulating effect of acupoints/meridians for the visceral function^[35–37]^ On 1 hand, we hypothesize that the change in microcirculatory characteristics of the Heart meridian between the healthy control group and CSAP group is more significant than that of the Lung meridian. Thus, the specificity for the meridian-visceral association will be investigated by comparing the microcirculatory difference between the Heart and Lung meridians in the healthy control group and CSAP group. We present such a comparison (healthy control group vs CSAP group) to verify the sensitization phenomena of meridians under pathological circumstances as well as the specificity of meridian-visceral association.

On the other hand, we hypothesize that the change in microcirculatory characteristics in relevant sites of the stimulated meridian is more significant than that of the non-stimulated meridian in the healthy control group. Thus, the specificity for the site-to-site association will be explored by comparing the microcirculatory change between the Heart and Lung meridians by performing moxibustion in the Heart meridian and Lung meridian, respectively. It should be noted that moxibustion intervention is applied only in the healthy control group rather than the CSAP group. By such a study design and comparison, we attempt to confirm whether meridians are not only sensitized in pathological conditions but also activated in physiological state, which is an important issue to be solved in meridian researches.

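### Section 2.10 tests the moxibustion response before against after, although the stated hypothesis compares the stimulated with the non-stimulated meridian and no unheated recording of equal length exists

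*Protocol article*

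**What the plan says.** **Analysis.** Section 2.10 states: "Repeated measures ANOVA will be used to assess change in continuous variables before and after intervention". It continues with t-tests within and between groups: "The paired samples *t*-test will be used to compare the changes within the groups, whereas the independent samples t-test will be employed for comparisons between" (sentence cut short here). The threshold is given as "A *P* value of less than .05 will be considered statistically significant". No meridian, site or session factor is named.

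**Recordings.** Section 2.6.1 sets two moxibustion sessions at least a day apart, one at HT3 (Heart) and one at LU5 (Lung). The recording covers "5 minutes before moxibustion, 15 minutes during moxibustion and 5 minutes after removal of moxibustion". Each session has three probes: the forearm midpoint of the stimulated meridian, and the midpoint and elbow point of the other. For the groups recorded without heat, at HT7, HT3, LU9 and LU5, the text says: "The blood flow curve and PU will be recorded for 5 minutes".

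**Hypothesis and conclusion.** The Discussion expects a larger change on the stimulated than on the non-stimulated meridian. Referring to that design and comparison, it then says: "we attempt to confirm whether meridians are not only sensitized in pathological conditions but also activated in physiological state".

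**Who is heated.** The Abstract and section 2.6.1 give moxibustion to the healthy intervention group. The opening of section 2.6 and the Discussion give it to the healthy control group.

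**The concern.** The named test and the stated hypothesis do not match. A before-after test asks whether perfusion at a site changed during the session. The hypothesis asks whether it changed more on one meridian than on the other.

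The difference matters because everyone who is recorded for the full session is heated. Lying still, relaxing or a settling probe could change perfusion without any effect of moxibustion, and no recording in the design would show it. If the activation statement rested on the before-after test, a significant time effect would not support it.

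The link between hypothesis and test cannot be left to the analysts' judgement either. Section 2.5 has the analysis done by third-party statisticians who are kept unaware of the protocol, so they may see section 2.10 without the Discussion.

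**Working it through.** **Inputs from the protocol article**
- Participants per group: 40 (section 2.2; 3 × 40 = 120 agrees with the stated total). No effect size, SD or power is given, so there is no sample-size formula to reproduce.
- Heated session: 5 + 15 + 5 = 25 minutes recorded, after 15 minutes of supine rest, so 40 minutes supine (section 2.6.1).
- Unheated recording: 5 minutes, not at the forearm midpoints (section 2.6.1).
- Significance level 0.05 (section 2.10); two-sided is assumed.

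**Assumed:** the drift *d*, in SDs of the within-person change.

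**Step 1. Before-after test at one site, moxibustion doing nothing.** The paired t-test stands in for the two-period case of the ANOVA. With n = 40 the test has 39 degrees of freedom and noncentrality λ = d√40 = 6.325 d. With c the 97.5% point of t on 39 degrees of freedom,

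P(significant) = 1 − F(c; 39, λ) + F(−c; 39, λ), where F is the noncentral t distribution function.

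| Assumed drift d | λ | P(significant) |
|---|---|---|
| 0 | 0 | 5.0% |
| 0.10 | 0.63 | 9.5% |
| 0.20 | 1.26 | 23.5% |
| 0.25 | 1.58 | 33.8% |
| 0.30 | 1.90 | 45.7% |
| 0.50 | 3.16 | 86.9% |

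**Step 2. What the contrasts cancel.** Let session A heat the Heart meridian and session B the Lung meridian. Let the changes at the two midpoints be A_H, A_L, B_H and B_L, with drift d_H and d_L at the two sites.

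- Same session, stimulated minus non-stimulated: A_H − A_L has drift d_H − d_L. This is zero only if the sites drift alike.
- Same midpoint across sessions: A_H − B_H has drift d_H − d_H = 0.
- Meridian by session: (A_H − A_L) − (B_H − B_L) has drift (d_H − d_L) − (d_H − d_L) = 0. Drift specific to one session but shared by both sites also cancels here.

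The last two need each site's own drift to be the same in both sessions.

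**Step 3. Simulation, 20,000 trials of 40 people, no moxibustion effect.** Entries are the share of trials significant at 5%.

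| d_H, d_L | Correlation between sites | Before-after | Same-session contrast | Same midpoint, across sessions | Meridian by session |
|---|---|---|---|---|---|
| 0.5, 0.5 | 0 | 86.9% | 5.1% | 5.0% | 4.9% |
| 0.5, 0.5 | 0.5 | 86.8% | 4.5% | 5.0% | 4.9% |
| 0.5, 0.2 | 0 | 86.7% | 25.4% | 4.9% | 5.0% |
| 0.5, 0.2 | 0.5 | 87.1% | 45.4% | 4.8% | 5.0% |

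**Step 4. What no contrast recovers.** Suppose heat raises both midpoints by the same amount g in both sessions. The meridian-by-session contrast is then (g − g) − (g − g) = 0, and the before-after change is g plus drift. With no unheated recording of that length, g and drift cannot be separated.

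**The case against.** A reader might infer that the trial judges the response only by before-after change, and that drift will therefore be reported as activation. The documents do not support this. The Discussion states the hypothesis as a difference in change between the meridians, and it ties the activation statement to that design and comparison. It nowhere says that an equal rise in both meridians would count as activation.

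The design also has real internal controls. Each session records two sites on the non-stimulated meridian, and both midpoints are recorded in both sessions. The 15 minutes of rest and the controlled temperature, humidity and time of day should reduce drift. The drift sizes above are assumptions. The paired t-test in section 2.10 could be read as comparing stimulated with non-stimulated change, repeated measures ANOVA can carry a meridian factor, and an analysis plan that is not shown may specify one. The authors call the trial a pilot.

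All of this narrows the point. What stands is that the one test section 2.10 names for change with the intervention is a before-after test, which does not address the stated hypothesis. An analysis plan could add the contrast, but it could not supply an unheated 25-minute recording.

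**Conclusion.** The point holds as a mismatch between the named test and the hypothesis. The design itself is able to test specificity.

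Used alone, the before-after test would be significant in 34% of trials at a drift of 0.25 SD and in 87% at 0.50 SD, with moxibustion doing nothing. These figures assume 40 complete participants, one site, a two-sided 5% test and the drift sizes shown. They illustrate the test's exposure and do not predict what this trial will find.

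The cross-session contrast stays near 5% under every drift pattern in the table, provided each site drifts alike in both sessions. The same-session contrast does so only if the sites drift alike; with drifts of 0.5 and 0.2 SD it is significant in 25% to 45% of trials. A general response to heat cannot be established from the recordings described.

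**What to change.** 1. In section 2.10, make the test of the moxibustion hypothesis the within-person stimulated-minus-non-stimulated change. The preferred form compares each forearm midpoint's change when its own meridian is heated with its change when the other is heated, across the two sessions (meridian by session by time).
2. Report the before-after ANOVA as descriptive.
3. In the Discussion, rest any statement about activation on that contrast, and say that an equal rise in both meridians cannot be told apart from drift.
4. Reconcile the statements on which healthy group receives moxibustion (the Abstract and section 2.6.1 against the opening of section 2.6 and the Discussion).

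All four are changes of wording and use recordings already planned. The downside is slight: a non-specific response to heat can no longer be claimed.

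Optional: lengthen the unheated healthy group's recording from 5 to 25 minutes, which adds 40 × 20 = 800 minutes, about 13.3 hours. This would give an unheated comparison only at LU5 and HT3, which are recorded on the non-stimulated meridian. The forearm midpoints are not among that group's sites, and its four probes occupy all four channels. Random allocation of the healthy adults to the two groups matters only if this comparison is made, and the trial is already described as ongoing.

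### The meridian-visceral hypothesis is a group-by-meridian contrast, but section 2.10 names no test of that contrast

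*Protocol article*

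**What the plan says.** The meridian-visceral hypothesis is in the Discussion (section 3) of the protocol article. The change in the "Heart meridian between the healthy control group and CSAP group is more significant than that of the Lung meridian". The same section, like the Abstract, says this will be investigated by "comparing the microcirculatory difference between the Heart and Lung meridians in the healthy control group and CSAP group".

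Section 2.10 lists the inferential methods:
- "Repeated measures ANOVA will be used to assess change in continuous variables before and after intervention".
- A paired samples t-test "will be used to compare the changes within the groups".
- For group comparisons, "whereas the independent samples t-test will be employed for comparisons between the groups".
- For skewed data, "Within-group/between-group comparison regarding data with skewed distribution is assessed using non-parametric test".
- A P "value of less than .05 will be considered statistically significant".

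Under section 2.6.1, control and CSAP participants each have one 5-minute recording at four sites: HT7 and HT3 (Heart), LU9 and LU5 (Lung). Both meridians are therefore measured in the same person. Section 2.2 sets 40 participants per group by precedent, with no effect size, standard deviation or power.

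**The concern.** The hypothesis concerns (CSAP minus control at Heart) minus (CSAP minus control at Lung). A test of either bracket alone does not test the difference between them. One meridian can cross the 0.05 line and the other miss it by chance while the true shifts are the same. The Discussion's wording, "between the healthy control group and CSAP group is more significant than that of the Lung meridian", makes it easy to answer the question by setting two p-values side by side.

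Specificity is the study's stated aim, and the Conclusions promise high-quality evidence for choosing acupuncture prescriptions. A specificity claim based on two separate tests would have no controlled error rate. It would also leave unused the within-person comparison, which removes any additive difference between patients and healthy adults that affects both meridians alike. Section 2.5 adds to the risk: the statisticians are to be blinded to the protocol, so they cannot be relied on to supply a contrast that the analysis section does not name.

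**Working it through.** **Step 1. Match each listed method to the hypothesis.**

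| Method in section 2.10 | Does it test group by meridian as worded? |
|---|---|
| Repeated measures ANOVA | No. It is defined for change around an intervention, and these two groups have one recording. Section 2.6 and part of the Discussion assign moxibustion to the healthy control group, against section 2.6.1 (these passages need reconciling). Even on that reading the CSAP group receives none, so a before/after analysis cannot compare the two groups. |
| Paired t-test | No. It works within one group. |
| Independent t-test | Only if applied to a Heart-minus-Lung difference, which is not stated. |
| Non-parametric tests | Same position as the two t-tests. |

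**Step 2. Inputs.** From the protocol: 40 CSAP against 40 controls (section 2.2) and alpha 0.05 (section 2.10; two-sided assumed). Not in the protocol, so assumed over a range: standardised shift d, identical in both meridians (no specificity), and within-person Heart-Lung correlation rho. There is no power figure in the plan to reproduce.

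**Step 3. False 'Heart-specific' rate from separate tests.** Let p be the power of one t-test with 40 per group. At rho = 0,

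P(Heart significant, Lung not) = p(1 − p).

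- d = 0.2: 0.143 × 0.857 = 0.12
- d = 0.44: 0.493 × 0.507 = 0.25, the maximum, because p(1 − p) peaks at p = 0.5
- d = 0.63: 0.795 × 0.205 = 0.16
- d = 0.8: 0.942 × 0.058 = 0.05
- d = 1.0: 0.993 × 0.007 = 0.007

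For rho above 0 the rate comes from simulation (bivariate normal, 40,000 trials per setting):

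| d | rho 0 | rho 0.5 | rho 0.7 | Direct contrast |
|---|---|---|---|---|
| 0.2 | 12% | 9% | 7% | about 5% |
| 0.44 | 25% | 17% | 13% | about 5% |
| 0.63 | 16% | 12% | 9% | about 5% |
| 0.8 | 5% | 4% | 3–4% | about 5% |
| 1.0 | under 1% | under 1% | under 1% | about 5% |

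The direct contrast is an independent t-test on each person's Heart value minus Lung value.

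**Step 4. Power of the direct contrast.** The difference has SD √(2(1 − rho)) in single-meridian SD units. For a Heart-only shift of 0.63 SD, power ≈ Φ(0.63 × √20 / √(2(1 − rho)) − 1.96), with 0.63 × √20 = 2.817:
- rho 0: Φ(2.817/1.414 − 1.96) = Φ(0.03) = 51%
- rho 0.5: Φ(2.817/1 − 1.96) = Φ(0.86) = 80%
- rho 0.7: Φ(2.817/0.775 − 1.96) = Φ(1.68) = 95%

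**Step 5. Scale.** If CSAP lowered flow by the same percentage at every site, raw PU would fall further where resting PU is higher. With an assumed 30% reduction, coefficient of variation 40% and rho 0.5 to 0.7, the contrast on raw PU rejects in about 29–42% of trials at a 1.5-fold resting ratio and about 7% at a 1.1-fold ratio. On log PU it rejects in about 5%.

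**The case against.** The best defence is that the protocol never states a rule of comparing p-values. Its description of the comparison, "comparing the microcirculatory difference between the Heart and Lung meridians in the healthy control group and CSAP group", can fairly be read as comparing the Heart-Lung difference across groups. The independent t-test of section 2.10, applied to that difference, is exactly the interaction test. This stands: the listed tools can answer the question, and the defect is that the variable is not named. A reader might infer that the plan commits itself to a faulty decision rule, or cannot test the interaction at all. Neither is supported.

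Other stronger readings also fail:
- The 25% is not the plan's error rate. It is the worst case over d, and the rate is at or below about 5% from d = 0.8 upwards.
- Separate site tests do not violate independence. A between-group test at one site uses one value per person, so it ignores no pairing.
- The 29–42% scale figure is not a further error of the plan. It belongs to a raw-PU contrast that the plan does not name and depends on an assumed resting ratio. In that same scenario the separate-test rule errs only about 2% of the time.

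It may also be said that an unseen analysis plan could name the contrast, and that the Discussion calls this a pilot. The first is possible. However, the article states both its hypothesis and its tests, and as stated they do not meet. Pilot status lowers the stakes but does not make a separate test of each meridian answer the question.

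**Conclusion.** The concern holds in a limited form. The hypothesis is a group-by-meridian contrast, and section 2.10 names no test of it. If specificity is inferred from separate Heart and Lung tests, equal true shifts would be reported as Heart-specific in under 1% to 25% of trials at 40 per group, against about 5% for the direct contrast. The range rests on assumed d from 0.2 to 1.0, rho from 0 to 0.7, normal data and two-sided 0.05. The plan can therefore yield a false claim of specificity; it has not been shown that it usually would. The choice of scale is a secondary point whose size depends on a resting ratio that the protocol does not give.

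**What to change.** In section 2.10, state that the meridian-visceral hypothesis is tested by one comparison between the CSAP and healthy control groups. For each participant, take the mean PU of HT7 and HT3 minus the mean PU of LU9 and LU5, and compare this difference by independent t-test or its non-parametric counterpart. State that specificity is concluded only from this contrast and its 95% confidence interval, and that single-site tests are descriptive.

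Analysing log PU is advisable, as the main or a sensitivity analysis, because a uniform percentage change can look like an interaction on raw PU when resting perfusion differs between meridians. If a mixed model on the four site values is preferred, it needs a participant-by-meridian random term. A participant intercept alone is not equivalent to the t-test on differences.

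The cost is a few sentences and no new data, since both meridians are already recorded in every participant. The downside is that specificity may be declared less often than by comparing separate tests, and power depends on the unknown correlation (51% to 95% in the example above).

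### Both hypotheses say an effect is larger on one meridian than the other, but the planned tests, applied site by site, do not test that difference, and no scale is fixed for it

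*Protocol article*

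**What the plan says.** All references are to the protocol article.

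- **Outcome.** Section 2.7 names the blood flow curve and "blood PU of relevant sites along the Heart and Lung meridians". Section 2.6.1 gives the unit: "microcirculatory flux, expressed as blood perfusion units (PU), will be assessed". No ratio, percentage or transformed scale is mentioned.
- **Hypothesis 1 (Discussion).** Lung serves as the comparator for Heart: "change in microcirculatory characteristics of the Heart meridian between the healthy control group and CSAP group is more significant than that".
- **Hypothesis 2 (Discussion).** This concerns moxibustion, with the non-stimulated meridian as comparator: "change in microcirculatory characteristics in relevant sites of the stimulated meridian is more significant".
- **Tests (section 2.10).** "Repeated measures ANOVA will be used to assess change in continuous variables before and after intervention". Paired t-tests serve within groups and independent t-tests between groups. For skewed data: "Within-group/between-group comparison regarding data with skewed distribution is assessed using non-parametric test". That test is not named. The significance level is 0.05.
- **Size (section 2.2).** Three groups of 40, chosen by analogy with similar studies.

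**The concern.** Each hypothesis concerns a difference between two effects. Hypothesis 1 is a group-by-meridian interaction. Hypothesis 2 is a within-participant comparison of two changes. A within-group or between-group test at one site answers another question: whether PU changed, or differs, at that site. A significant Heart result beside a non-significant Lung result is not evidence that the two effects differ.

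If the effects are compared directly, the answer depends on the scale. Equal percentage changes are unequal PU changes when the sites start from different levels. The article fixes neither the contrast nor the scale, and lets the choice of test depend on the observed distribution. Specificity is the stated aim of the trial, so a false or masked finding would bear on its main conclusion.

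**Working it through.** **Inputs.** From the article: 40 per group, level 0.05 (taken as two-sided), PU as the unit, and two crossed moxibustion sessions per participant in the healthy intervention group (section 2.6.1). The only stated figure to reproduce is 3 × 40 = 120, which holds; no effect size, SD or power is given. The article gives no baseline PU, SD, correlation or response model. Assumed for simulation: log-normal PU, log SD 0.45, between-site correlation 0.5, and the same percentage effect at both sites, so that there is no true specificity.

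**Step 1: what the tests address.** Write H and L for mean Heart and Lung PU. Site-wise tests examine H(CSAP) − H(control) and L(CSAP) − L(control) separately. Hypothesis 1 needs

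D = [H(CSAP) − H(control)] − [L(CSAP) − L(control)].

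With equal baselines and a 20% fall at both sites, site-wise rank tests give Heart significant and Lung not in about 17% of trials (16% to 17% between runs). This does not depend on unequal baselines and is not peculiar to rank tests. In a second set of runs (between-subject CV 0.5, correlation 0.5, equal baselines), the Heart-only result appeared as follows:

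| Common effect | t-tests | rank tests |
|---|---|---|
| ×0.7 | 8.0% | 7.4% |
| ×1.3 | 16.6% | 15.8% |
| ×1.5 | 4.2% | 3.3% |

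**Step 2: a direct contrast on PU, CSAP versus control.** Let the lower baseline be b, the higher k·b, and the common fall f. The absolute falls are f·b and f·k·b, so the contrast is off by f·b·(k − 1). With b = 10, k = 2 and f = 0.2, the falls are 2 and 4 PU, an apparent difference of 2 PU. On the log scale both changes are ln(0.8) and the difference is 0. Rejection rates of a t-test on Heart-minus-Lung PU:

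| Equal fall | ratio 1 | ratio 1.5 | ratio 2 |
|---|---|---|---|
| 20% | about 5% | 11–12% | 21–22% |
| 30% | about 5% | about 22% | about 46% |

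The log contrast stays at about 5% throughout. The second set of runs (effects ×0.7, ×1.3, ×1.5) gave 8–12%, 14–25% and 24–51% at ratios 1.25, 1.5 and 2, and about 5% on the log scale.

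**Step 3: direction.** The first table has Lung as the higher site. Nearly all its rejections say that Lung changed more: for the 20% fall, false Heart-over-Lung findings are 0.4% and 0.1% at ratios 1.5 and 2. Swapping the labels reverses this. The error follows the higher baseline.

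**Step 4: moxibustion.** Each midpoint lies on the stimulated meridian in one session and on the non-stimulated one in the other. Let the Lung midpoint have the higher baseline k·b, and let both midpoints rise by the fraction r. Stimulated minus non-stimulated is

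- Heart session: r·b − r·k·b = −r·b·(k − 1)
- Lung session: r·k·b − r·b = +r·b·(k − 1)

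The sum is 0. For an equal 20% rise (SD of log change 0.2), one session read alone rejects about 40% and 80% of the time at ratios 1.5 and 2 if log changes at the two sites correlate 0.5, and 27% and 60% if they are uncorrelated. Combined over both sessions the rate is about 5%.

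**Step 5: role of the rank fallback.** A Mann–Whitney test on the Heart-minus-Lung differences rejects 7–47% of the time over ratios 1.25 to 2, against 8–51% for the t-test. At a single site it gave the same decision on PU and log PU in every simulated trial. The fallback neither causes nor cures the scale artefact.

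**The case against.** The strongest reply has four parts.

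1. *The article condenses a fuller plan.* Derived variables and scale are often left to an analysis plan, and PU is named only as the unit of measurement. This stands for the scale: that raw PU will be analysed is an inference. It does not dispose of the point, because section 2.10 does name its tests and its remedy for skewness, and these do not match the hypotheses.
2. *The article does not say that tests run site by site.* The Abstract and Discussion say that Heart and Lung will be compared, and a repeated measures ANOVA could carry the interaction. This also stands, which is why Step 1 is conditional on site-wise use. But the ANOVA is assigned only to change before and after intervention, and hypothesis 1 has no intervention.
3. *Unequal baselines and proportional responses appear nowhere in the documents.* Correct. With equal baselines or additive effects, raw PU is not distorted. The log scale is itself an assumption: if moxibustion added 2 PU at both sites (Heart median 10, error SD 1), a one-session log contrast would falsely reject 76% and 99% of the time at ratios 1.5 and 2, while raw PU held 5%.
4. *The Discussion calls this a pilot and asks for caution.* That lowers the stakes, but the Conclusions still offer the results as a guide to acupuncture prescription.

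A reader might infer that raw PU with a rank fallback will manufacture meridian specificity. The documents do not support that. The mechanism is conditional, the fallback is not its source, the error may run against the Heart hypothesis, and it cancels across the crossed sessions.

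**Conclusion.** The point holds in limited form and is worth correcting. Applied at each site, the tests in section 2.10 do not test either specificity hypothesis. Under the stated assumptions a Heart-only pattern then arises in about 17% of trials with identical effects and equal baselines.

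If a direct contrast on PU is used, and if baselines differ and responses are proportional, the CSAP-versus-control comparison has a false rejection rate of about 11–12% to 46% over the 20% and 30% falls at ratios 1.5 and 2. Which meridian it favours is unknown without baseline data. For moxibustion the problem is confined to sessions read separately. The faults of the fallback are the missing contrast and a test chosen from the data.

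Confidence is medium. The mismatch between hypotheses and tests is read from the text; every rate rests on assumed SDs, correlations, ratios and effects.

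**What to change.** In section 2.10, drop the data-driven switch for the primary contrasts and prespecify one per-participant contrast for each hypothesis.

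- **Hypothesis 1:** log(Heart PU) minus log(Lung PU), compared between the control and CSAP groups. State how the two sites on each meridian are combined.
- **Hypothesis 2:** log(during or after ÷ before) at the midpoint on the stimulated meridian, minus the same at the midpoint on the non-stimulated meridian, combined over both sessions within participant. Choose during or after in advance.

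Report ratios with 95% confidence intervals. Add a rank test of the same contrast and a raw-PU analysis as sensitivity checks; the latter shows whether the conclusion depends on scale.

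The cost is wording only, with no new data. Results will read as percentage differences rather than PU. The log scale assumes roughly proportional effects; if effects are additive, the log contrast could mislead instead. This matters most for hypothesis 1, which has no crossed session to cancel a fixed site difference.
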